### Follow-up

After baseline visit, all participants will receive follow-up visits at 1, 3, 6, 9, 12, and 24 months, as scheduled (see Fig. 2 for SPIRIT figure). The primary and secondary outcome measures will be monitored during the whole study period. Most laboratory tests in the treatment arm will be tested at baseline and at 1, 3, 6, and 12 months, while in the control arm most tests will only be conducted at baseline. Platelet aggregation rate and hypersensitivity C-reactive protein level will be measured in both the treatment and control arm at baseline and in the third month in one or two selected centers in Shanghai to explore the potential effects of GXNT on platelet aggregation and inflammation.

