## Background

Millions of patients worldwide receive percutaneous coronary intervention (PCI) for treatment of coronary artery disease [1, 2], and treatment with dual antiplatelet therapy (DAPT) for 12 months after PCI has been considered standard care for preventing stent thrombosis and major adverse cardiovascular events (MACEs). Concerning the possibility of late or very late stent thrombosis, which is frequently associated with myocardial infarction, and may be fatal [3], researchers have conducted plenty of studies to explore the benefits and risks of prolonged (>12 month) DAPT [4–9]. Among those, the DAPT trial is the largest and sufficiently powered trial, and demonstrated that, compared with 12 months’ DAPT, an additional 18 months treatment with DAPT  further reduced the risk of stent thrombosis (hazard ratio 0.29, 95% confidence interval 0.17 to 0.48, *p* < 0.001) and MACE rate (hazard ratio 0.71, 95% confidence interval 0.59 to 0.85, *p* < 0.001), establishing the antithrombotic benefits of extended DAPT (>12 months) in post-PCI patients [9]. Later, a systematic review comparing extended DAPT (>12 months) with standard 12 month therapy also confirmed the benefits of extended DAPT, demonstrating that extended DAPT significantly reduced the risk of myocardial infarction (0.53, 95% confidence interval: 0.42 to 0.66) and stent thrombosis (0.33, 95% confidence interval: 0.21 to 0.51) [10]. However, all the antithrombotic benefits of extended DAPT are accompanied by increased bleeding risk, which has raised broad concerns. For example, in the DAPT trial [9], researchers found that 30 months of DAPT led to a 0.9% absolute increase in moderate to severe bleeding risk and a risk–benefit analysis showed that prolonged DAPT, annually, resulted in three fewer stent thromboses and six fewer myocardial infarctions at the cost of five more major bleeds per 1,000 patients. Notably, a recently published meta-analysis of 12 trials, comprising over 34,000 patients receiving different durations of DAPT, revealed that bleeding was an independent predictor of 1-year mortality and that longer duration of DAPT was associated with more bleeding-related deaths [11]. Besides, coronary artery disease itself is an exceedingly costly disease, costing a total of $316.6 billion annually in the USA [1], and prolonged application of the P2Y12 inhibitors will definitely add to the economic burden of both the nation and individuals. Thus, it is urgent to find an alternative drug that is as effective, but safer and more economic than P2Y12 inhibitors.

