## Methods

### Objectives and design

This study is a prospective, multicenter cluster randomized controlled trial aiming to explore whether the addition of GXNT to conventional treatment, including aspirin, will decrease MACEs without increasing bleeding risk for post-PCI patients who switch to aspirin monotherapy after the standard 12 months DAPT. An economic evaluation with 360 participants will be carried out alongside this trial in six of the 36 centers to assess the long-term cost-effectiveness of GXNT. The selection of the six centers takes both area and hospital type into account; three centers in Beijing and three centers in Hangzhou will be chosen. This study follows the international recommendations for interventional trials [21]. (See the SPIRIT checklist in Additional file 1.)

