### Safety outcomes and compliance monitoring

The incidence of bleeding defined according to the Bleeding Academic Research Consortium definitions [24], any adverse events or serious adverse events, and compliance of the participants will be closely monitored and recorded during the whole trial period. If necessary, treatment will be ceased and patients will be withdrawn according to the nature of adverse events or serious adverse events. Compliance of the participants with the intervention is assessed by counting tablets of GXNT and reviewing tablet log records.

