**Fig. 2 Fig2:**
[figure not shown]
Trial schedule. ^*^The Seattle Angina Questionnaire (SAQ) and Short Form-36 (SF-36) will be only measured in the six hospitals selected for economic evaluation. ^#^The platelet aggregation and hypersensitivity C-reactive protein (hs-CRP) are to be tested in both control and treatment arm in one or two centers in Shanghai. ^a^Major adverse cardiovascular and cerebrovascular events (MACEs) include all-cause death, cardiovascular death, non-fatal myocardial infarction, stent thrombosis, revascularization, ischemic stroke, and rehospitalization for unstable angina. ^b^Routine tests include complete blood count, urinalysis, and stool tests. ^c^Includes levels of aspartate aminotransferase, alanine aminotransferase, alkaline phosphatase, gamma-glutamyl transpeptidase, total bilirubin, and direct bilirubin. ^d^Coagulation function includes levels of prothrombin time, thrombin time, international normalized ratio, activated partial thromboplastin time, and fibrinogen

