Data analysis will be conducted by Nanjing Medical University. All analyses will be performed on the individual level with adjustment for clustering and all available data from the dropouts will be included in the analysis up to the time of dropout where possible. All statistical hypothesis tests will be two-tailed and performed at a 5% significance level. Continuous variables will be presented as means and standard deviation, median or interquartile range. Categorical variables will be expressed as frequencies and percentages. Normality of relevant data will be examined using the Shapiro–Wilk test. Cluster-adjusted baseline differences between arms will be analyzed using the independent Student’s *t* test or the Mann–Whitney test for continuous variables and the Pearson *χ*^2^ test for categorical variables. All outcome measures, including the primary outcome measure, will be analyzed using a generalized linear mixed-effect model with the fixed effect being the intervention and the random effect being hospitals, to account for the potential correlation of outcomes within each hospital. Moreover, we will calculate the absolute rate reduction with 95% confidence interval as a crude estimate of the rate difference between the treatment and control groups by using the Mantel–Haenszel method. The number needed to treat for the primary outcome measure as the inverted absolute rate reduction will also be calculated. Efficacy outcomes are to be analyzed according to the intention-to-treat principle.

Safety outcomes will be assessed among all randomized patients except those who do not take any study medication or who have no safety records. The safety outcomes will be summarized and analyzed using the approach outlined.

Missing data will be accounted for by the modern imputation methods and all analysis will be conducted using SAS software version 9.4 (SAS Institute, Cary, NC, USA).

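### Most laboratory tests are repeated after baseline only in the GXNT arm, so laboratory-detected adverse events cannot be compared fairly between arms; the bleeding objective should rest on a confidence interval, not a non-significant test

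*Protocol article*

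**What the plan says.** All references are to the protocol article.

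- **Laboratory schedule (Follow-up).** For GXNT: "Most laboratory tests in the treatment arm will be tested at baseline and at 1, 3, 6, and 12 months". For control: "while in the control arm most tests will only be conducted at baseline". The stated exception is platelet aggregation and hs-CRP, measured in both arms at baseline and month 3 in one or two Shanghai centres.
- **Test content (Fig. 2 footnotes).** "Routine tests include complete blood count, urinalysis, and stool tests"; liver and coagulation panels are listed as well.
- **Clinical visits (Follow-up).** These are common to both arms: "all participants will receive follow-up visits at 1, 3, 6, 9, 12, and 24 months".
- **Safety outcomes (Safety outcomes and compliance monitoring).** "The incidence of bleeding defined according to the Bleeding Academic Research Consortium definitions", together with any adverse or serious adverse events, recorded throughout the trial.
- **Objective (Objectives and design).** The question is whether adding GXNT "will decrease MACEs without increasing bleeding risk for post-PCI patients".
- **Analysis (Sample size and data analysis).** "All statistical hypothesis tests will be two-tailed and performed at a 5% significance level". Safety outcomes follow the approach set out for the other outcomes. That approach is a mixed model with hospital as random effect, plus a Mantel–Haenszel rate difference with a 95% interval, which the article calls crude.
- **Blinding (Allocation; Data management and monitoring).** Patients and caregivers know the treatment; outcome assessors and analysts do not. The endpoint committee's stated remit is MACEs.

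**The concern.** A comparison of adverse-event rates needs the same opportunity to detect an event in each arm. Here that opportunity differs by design for anything found by routine laboratory work, and no model can recover tests that were never done in the control hospitals.

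The consequence runs in two directions. Extra testing adds recorded events in the GXNT arm, so GXNT may look more harmful than it is. Because that is known in advance, a genuine excess of, say, liver abnormalities or falls in haemoglobin can be put down to testing. Either way the comparison does not answer the safety question.

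The second issue concerns inference. Half of the stated objective is the absence of a bleeding increase, while the hypothesis tests are two-sided tests for a difference. Failing to reject in such a test is not evidence of no increase, and the trial was sized for MACE, not for bleeding.

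**Working it through.** **1. Detection opportunity.** Setting the schedules side by side:

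- Scheduled post-baseline laboratory rounds, most tests: GXNT 4 (months 1, 3, 6, 12); control 0.
- Scheduled clinical visits after baseline: 6 in each arm (months 1, 3, 6, 9, 12, 24).

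A bleed or adverse event that the patient notices or reports has the same six scheduled contacts in both arms. One visible only in a blood, urine or stool result has a routine route to detection only with GXNT. Blinded assessors do not cure this, because they can classify only what has been found. The document gives neither the rate of such events nor the share that testing would uncover, so no size can be attached to the bias.

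**2. The plan's own sample size.** Inputs from Sample size and data analysis: 21% against 21% × (1 − 0.21) = 16.59%, two-sided alpha 0.05, power 0.80, ratio 2:1, ICC 0.002, 90 per cluster.

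- Pooled rate: (0.21 + 2 × 0.1659)/3 = 0.1806.
- Control n = [1.96 × √(0.1806 × 0.8194 × 1.5) + 0.8416 × √(0.21 × 0.79 + 0.1659 × 0.8341/2)]² / 0.0441² = 912; total 2736.
- Design effect: 1 + (90 − 1) × 0.002 = 1.178; 2736 × 1.178 = 3223.

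The stated 3240 is reproduced (power 80.2% at 1080/2160). It is a calculation for MACE only.

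**3. What a non-significant bleeding test would mean.** Effective sizes: 1080/1.178 = 916.8 (control) and 2160/1.178 = 1833.6 (GXNT). The document gives no control bleeding rate, so 1% to 2% is assumed, and the ICC for bleeding is assumed equal to the MACE value. As a yardstick only, take a true increase of 0.9 points, from the Background: "30 months of DAPT led to a 0.9% absolute increase in moderate to severe bleeding risk".

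Worked case, control 1%, GXNT 1.9%:

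- SE under the alternative = √(0.01 × 0.99/916.8 + 0.019 × 0.981/1833.6) = 0.00458.
- Unpooled test: 0.009/0.00458 = 1.97; power = Φ(1.97 − 1.96) ≈ 50%.
- Pooled test: pooled rate 0.016; null SE = √(0.016 × 0.984 × (1/916.8 + 1/1833.6)) = 0.00508; power = Φ((0.009 − 1.96 × 0.00508)/0.00458) ≈ 42%.

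Chance of missing the 0.9-point increase:

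| Control rate (assumed) | Unpooled | Pooled |
|---|---|---|
| 1% | 50% | 58% |
| 1.5% | 61% | 67% |
| 2% | 68% | 72% |

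For the pooled test over the same 1% to 2%, the range is 52% to 68% with ICC 0 and 73% to 82% with ICC 0.01.

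**4. What the interval would show instead.** Half-width at equal rates p = 1.96 × √(p(1 − p)(1/916.8 + 1/1833.6)): 0.79 points at 1%, 0.96 at 1.5%, 1.11 at 2%. The interval tells the reader which increases remain possible, and that depends on the bleeding rate actually seen. A p-value above 0.05 does not give this.

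**The case against.** The strongest points on the other side are these.

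- **Overt bleeding is equally sought.** Visits are identical, one published bleeding definition applies, and outcome assessors are blinded. This stands. A reader might infer that the whole bleeding comparison is biased, but the document does not support that: nothing says a routine result alone counts as a bleed. The secure part is laboratory-detected events.
- **The text says most tests, not all.** The schedule chart is not reproduced in the text available, and the footnotes do not tie each panel to an arm. This stands as a limit on naming exactly which tests are affected; the asymmetry itself is stated outright.
- **The direction is conservative for the drug.** Largely true: extra testing inflates GXNT events. It still leaves a real excess open to being explained away.
- **The article never says non-significance will be read as no increase, and it plans a 95% interval.** Both are correct. A margin may also sit in an analysis plan that is not shown, so its absence here is not a fault. What remains is that the article pairs a no-increase objective with difference tests and does not tie the objective to the interval, which it describes as crude.
- **The 0.9-point figure is a poor margin.** Agreed. It concerns moderate to severe bleeding on 30 months of DAPT, and the Background cites it as an example of a concern, not as a limit of acceptability. It serves here only to show what the test could miss. At a 1% rate, equal observed rates would exclude it (half-width 0.79), so not every null result would be compatible with it.

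**Conclusion.** The concern holds in a limited form. Laboratory-detected adverse events are ascertained unequally by design and are then compared between open-label arms as if they were not. Clinically overt bleeding is less affected. The primary MACE analysis, with blinded adjudication, is not touched by this point.

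The amount of bias cannot be derived from the document. A reader might want a probability of a spurious excess, but that would require inventing both the base rate and the number of events added by testing.

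On inference, the supportable statement is that a two-sided 5% test would miss a true 0.9-point increase in roughly 50% to 72% of trials. This assumes control bleeding of 1% to 2%, an ICC of 0.002 for bleeding, 1080 and 2160 evaluable patients, and a normal approximation; the spread includes the choice between unpooled and pooled variance.

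This should be fixed. It limits what the trial can say about safety without invalidating its main result.

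**What to change.** - Restrict the between-arm comparison of bleeding and adverse events to clinically overt or symptomatic events ascertained in the same way at the common visits.
- Record for each event how it was detected (symptom or patient report, clinical visit, scheduled laboratory test, other). This needs one case-report-form field, in place when events are recorded, because it is hard to reconstruct later.
- Report events found only by scheduled GXNT-arm laboratory tests descriptively, as single-arm data.
- State that the bleeding part of the objective will be judged from the cluster-adjusted 95% confidence interval of the risk difference, and that a non-significant two-sided test will not by itself be taken as showing no increase.

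The cost is protocol and analysis wording plus the one field; no extra patients or visits are needed. The downside is that laboratory safety then has no control comparison. At the planned size the interval may also be too wide to support a firm no-increase statement, and the report should then give the interval without that claim.

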### Allocation

Thirty-six participating hospitals (clusters) with 3600 patients are firstly stratified by type of medication delivery (Western medical or traditional Chinese medicine hospitals), and then hospitals in each stratification are randomly allocated in a 2:1 ratio by a computer-generated, centrally controlled randomization schedule to treatment (24 hospitals with 2400 patients) or control (12 hospitals with 1200 patients) arms (see Fig. 1). All patients from one cluster will receive same intervention. Though the patients and caregivers are not blinded, the outcome assessors and data analysts are to be blinded to treatment allocation to minimize potential bias.

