### Sample size and data analysis

As little data on MACE rate in post-PCI patients who switch from DAPT to aspirin for about 12 months is available, we have to calculate the sample size according to the results of other studies. One registry trial reported that the annual rate of death or myocardial infarction was approximately 4.7%/year for patients who underwent successful implantation of at least one drug-eluting stent and did not received prolonged DAPT [25]. Another retrospective study indicated that the 2 year composite rate of mortality, reinfarction, and target vessel revascularization for patients undergoing primary PCI after acute myocardial infarction was 23% to 30% [26]. Though participants in our trial may have a lower rate of mortality, reinfarction, and target vessel revascularization than the retrospective study, taking other components into account, including stent thrombosis, ischemic stroke, and re-admission for unstable angina, we estimate the 12 month rate for the primary outcome measure in patients taking aspirin alone might be 21%, and that GXNT will reduce the incidence by 21%. A statistic power of 0.8 and a type I error rate of 0.05 (alpha) are chosen. According to a previous study, we assume the coefficient of intracluster correlation to be 0.002 [27] and we expect to recruit 90 patients from each cluster (hospital). Thus, a total of 3240 patients with 36 clusters (hospitals) will be needed. Considering a dropout rate of 10%, a minimum of 3564 patients is needed; for convenience of randomization, we decided to recruit 3600 patients (100 patients per hospital) and 36 hospitals (2400 patients and 24 clusters in the treatment arm, 1200 patients and 12 clusters in the control arm). Considering the uncertainty of the MACE rates in the study population, an interim analysis will be conducted when one-third of expected MACEs occur and the sample size will be adjusted according to the results of the interim analysis.

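### Platelet aggregation and hs-CRP are to be compared between arms in one or two Shanghai hospitals, but hospitals are the unit of randomisation, so the GXNT effect cannot be separated from the hospital

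*Protocol article*

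**What the plan says.** Four places in the protocol article bear on this.

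- **Allocation.** The hospital is the unit of randomisation: "hospitals in each stratification are randomly allocated in a 2:1 ratio by a computer-generated, centrally controlled randomization schedule". Within a hospital there is no mixing: "All patients from one cluster will receive same intervention".
- **Outcome measures.** hs-CRP and platelet aggregation rate are listed as other efficacy outcomes, after the primary and secondary ones.
- **Follow-up.** The two biomarkers "will be measured in both the treatment and control arm at baseline and in the third month", and this is to be done "in one or two selected centers in Shanghai to explore the potential effects of GXNT on platelet aggregation and inflammation". The footnote to Fig. 2 repeats that they "are to be tested in both control and treatment arm in one or two centers in Shanghai".
- **Sample size and data analysis.** "All outcome measures, including the primary outcome measure, will be analyzed using a generalized linear mixed-effect model", with intervention as the fixed effect and hospital as the random effect. No exception is made for the biomarkers.

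**The concern.** The number of centres, the presence of both arms, the time points and the purpose are all stated, and stated twice. They do not fit the allocation rule or the analysis model. A single centre can supply one arm only. Two centres can supply both arms, but then every difference between the two hospitals is also a difference between the arms: case mix, co-treatment, sample handling, and the laboratory if assays are run locally.

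Antiplatelet action is the mechanistic rationale in the Background and Discussion, and this is the only comparison of platelet function that the article describes. A one-versus-one hospital result could therefore be read as mechanistic support that it cannot give. A later analysis plan cannot repair this, because the missing information is hospitals, not model detail.

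**Working it through.** **The plan's own figure.** The article gives no sample size for the biomarkers. Its main calculation does show that it counts the hospital as a source of variance.

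- Inputs: control rate 0.21; 21% relative reduction, so 0.21 × 0.79 = 0.1659; 2:1 allocation; two-sided 5%; power 0.80; ICC 0.002; 90 patients per hospital.
- The pooled-variance two-proportion formula gives 912 control + 1824 GXNT = 2736.
- Design effect: 1 + (90 − 1) × 0.002 = 1.178. Then 2736 × 1.178 = 3223, and 3223 / 90 = 35.8 hospitals, rounded up to 36 × 90 = 3240, as stated.

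The same logic has to apply to the biomarkers.

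**Model.** For patient i in hospital j, with T = 1 for GXNT and 0 for control:

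y(ij) = μ + β·T(j) + u(j) + e(ij), with Var(u) = σ²u and Var(e) = σ²e.

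Between-hospital degrees of freedom for a two-arm contrast = hospitals − 2.

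| Hospitals measured | Between-hospital df | Consequence |
|---|---|---|
| 1 | none | only one arm present, no contrast |
| 2 (one per arm) | 2 − 2 = 0 | β cannot be separated from u |
| 4 (two per arm) | 4 − 2 = 2 | t critical 4.30 |
| 36 (whole trial) | 36 − 2 = 34 | t critical 2.03 |

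The 2-df value follows from the closed form t = a·√(2/(1 − a²)) with a = 0.95: 0.95 × √(2/0.0975) = 4.30.

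**Two hospitals.** The only between-arm information is D, the difference between the two hospital means. It has expectation β over repeated randomisation, but in the one realised pair it equals β + u(1) − u(0) plus sampling error. Its variance is 2σ²u + 2σ²e/m. With one hospital per arm, nothing in the data informs σ²u, so no valid standard error for β exists.

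**Does ignoring the hospital help?** A test that uses only within-hospital variance understates Var(D) by the factor [1 + (m − 1)ρ]/(1 − ρ), where ρ is the ICC. Its true type I error is 2·[1 − Φ(1.96/√factor)]. With m = 90:

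| Assumed ICC | Factor | Type I error of a nominal 5% test |
|---|---|---|
| 0.002 | 1.178/0.998 = 1.18 | 7% |
| 0.01 | 1.89/0.99 = 1.91 | 16% |
| 0.05 | 5.45/0.95 = 5.74 | 41% |
| 0.10 | 9.90/0.90 = 11.0 | 55% |

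The article gives no ICC for either biomarker; its 0.002 is for the primary outcome. It also does not say how many patients per centre are assayed. The table is therefore a range under assumptions.

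**Does the baseline value help?** Change scores remove a stable difference in level between hospitals. They leave change specific to a hospital over the three months, such as assay drift or changes in co-treatment. With one hospital per arm, that change is still aliased with arm, and the degrees of freedom are still 0.

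**Why spreading assays helps.** With h hospitals per arm and a fixed N assays per arm, Var(D) = 2σ²u/h + 2σ²e/N. The second term does not depend on h. Going from one to two hospitals per arm halves the first term at the same assay count and gives 2 df instead of 0.

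**The case against.** Several things can be said for the plan.

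- **The biomarkers are exploratory and third-tier.** True, and it limits the importance of the point. It does not make the comparison estimable.
- **The wording could mean one or two centres per arm.** This is less natural, but possible. One per arm is again two hospitals with 0 df; two per arm leave 2 df and a t critical value of 4.30. The wording needs clarifying either way.
- **The article is condensed.** That excuses missing detail. Here the details are given, and they conflict with Allocation and with the stated model.

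Two stronger readings are tempting but not supported.

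- A reader might infer that the Shanghai centres could both fall in the same arm by chance. The text says that the centres are selected and that both arms are measured, so the evident intent is to have both. The objection rests on one hospital against one, and needs no probability.
- A reader might infer that the six economic-evaluation centres are picked without regard to arm, since "three centers in Beijing and three centers in Hangzhou will be chosen" and only area and hospital type are mentioned. The article does not say that these are the only criteria, and the centres may be chosen after allocation. How many come from each arm is a detail that an article may leave to the full protocol. At most, it is a question to ask.

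**Conclusion.** The point stands for platelet aggregation and hs-CRP. With one centre, the stated two-arm measurement is impossible. With two centres on the natural reading, arm equals hospital, 0 between-hospital degrees of freedom remain, and the prescribed mixed model cannot estimate the GXNT effect. This follows from the article's own text and needs no outside assumption. Only the type I error range (7% to 55% for ICCs of 0.002 to 0.10 with 90 patients per hospital) rests on assumed values, and the conclusion does not depend on it. On the per-arm reading, the most that can be had is 2 df.

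It should be corrected, but it does not threaten the trial. Nothing here touches the primary, secondary or safety analyses, which draw on all 36 hospitals ("2400 patients and 24 clusters in the treatment arm, 1200 patients and 12 clusters in the control arm").

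**What to change.** Change Follow-up, the Fig. 2 footnote, and Sample size and data analysis together, in one of two ways.

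1. **Describe only.** Restate the two biomarkers as a within-arm description of change from baseline to month 3 in the selected centre or centres. State that there will be no between-arm test and no causal claim, and exempt them from the mixed model. Cost: a weaker exploratory claim, and no extra work.
2. **Keep the comparison.** Spread the same number of assays over at least two hospitals per arm. Keep the random hospital effect, use small-sample degrees of freedom (for example Kenward–Roger), and state that precision is limited by the number of hospitals. Cost: assay set-up at a few more sites. Two per arm is a bare minimum; each added hospital brings one more degree of freedom.

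In either case, state whether one or two means in total or per arm. Neither option alters the allocation scheme, the treatment or the trial size. Separately, and only as a query, the sponsor could be asked how many of the six economic centres come from each arm.
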